## Methods and Analysis

### Study Design

This is a single-center, randomized, participant- and outcome-assessor-blinded, sham-controlled, clinical study. The study will be conducted at the Tongji Hospital, affiliated with Tongji Medical College, Huazhong University of Science and Technology (HUST) in Wuhan, China. An adaptive sample size of 154–500 patients will be recruited from the ICU ward within 24 h of their ICU admission. The total trial period comprises 24 h of baseline assessment, 6 days of postrandomization treatment, and a 22-day follow-up period. Written informed consent will be obtained before randomization. ICU-attending physicians will provide detailed informed consent to patients or their legal guardians under ICU monitoring. Upon confirmation of eligibility, patients will be randomized into either the EA group or the sham-EA group. A complete treatment protocol requires the following: (1) the initial acupuncture treatment should be administered within 12 h post-randomization, and (2) six sessions of EA or sham EA should be conducted once daily for 30 min per session. The study protocol strictly adhered to the Standard Protocol Items: Recommendations for Interventional Trials (SPIRIT) reporting guideline [27]. The trial flowchart is presented in Fig. 1, with detailed procedures and schedules outlined in Table 1.

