**Fig. 1 Fig1:**
[figure not shown]
Study flow diagram

**Table 1 Tab1:** Schedule of recruitment, interventions, and measures

	Time point (days)											
	Baseline		Treatment						Follow-up			
	–1	0	1	2	3	4	5	6	7	8	9	28

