**Measures**												
SOFA score	** × **		** × **	** × **	** × **	** × **	** × **	** × **	** × **	** × **	** × **	
SOFA score of each system	** × **		** × **	** × **	** × **	** × **	** × **	** × **	** × **	** × **	** × **	
SOFA score components	** × **		** × **	** × **	** × **	** × **	** × **	** × **	** × **	** × **	** × **	
All-cause (ICU) mortality												** × **
ICU/hospital-free days												** × **
Ventilator-free time												** × **
Vasopressor-free days												** × **
CRRT-free days												** × **
Liquid equilibrium parameter	** × **		** × **	** × **	** × **	** × **	** × **	** × **				
Serum biomarkers and related cellular assays	** × **				** × **				** × **			
AEs			** × **	** × **	** × **	** × **	** × **	** × **				

EA, electroacupuncture; SOFA score, Sequential Organ Failure Assessment score; ICU, intensive care unit; CRRT, continuous renal replacement therapy; AEs, adverse events

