#### EA Group

Participants in the EA group will receive acupuncture at bilateral acupoints ST36 and GB34. In patients in the supine position, after sterilization, sterile adhesive pads will be placed on the bilateral ST36 and GB34. Afterward, the acupuncturist inserted sharp needles into the skin of acupoints ST36 and GB34 approximately 20 to 30 mm through the adhesive pads, followed by manual manipulation of each needle for 10 s to induce sensation of deqi (a composite of sensations including soreness, numbness, distention, heaviness, and other sensations). Afterward, paired electrodes from the EA apparatus will be attached transversely to the needle handles at bilateral ST36 and GB34. EA stimulation lasted for 30 min, with a continuous wave of 10 Hz and a current intensity of 1 mA (preferably with the skin around the acupoints shivering mildly without pain). Participants will receive EA sessions once daily for 6 consecutive days.

Sterile, disposable Hwato-type acupuncture needles (Suzhou Medical Supplies Factory Co., Ltd., China) 0.30 mm in diameter and 40 mm in length were used. EA stimulation was delivered using a Hwato SDZ‑V EA device.

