#### Secondary Endpoints

Participants will be followed up until day 28 after randomization. Secondary outcomes include the following: (1) all-cause mortality on day 28; (2) all-cause ICU mortality on day 28; (3) ICU-free days to day 28; (4) hospital-free days to day 28; (5) ventilator-free days to day 28; (6) vasopressor-free days to day 28; (7) continuous renal replacement therapy (CRRT)-free days to day 28; (8) changes in SOFA total scores at days 8 and 9; (9) changes in each item of the SOFA score (i.e., the ratio of arterial oxygen partial pressure to fractional inspired oxygen ratio (PaO_2_/FiO_2_), ventilator use, platelet counts, total bilirubin, mean arterial pressure, vasopressor use, Glasgow Coma Scale score, creatinine level, and urine volume) from baseline to day 9; (10) changes in serum biomarkers and related cellular assays on day 3 and day 7 compared with baseline; and (12) changes in the liquid equilibrium parameters, including daily fluid intake, output and fluid balance from baseline to day 6 after randomization.

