### Safety Assessments

In reference to the literature concerning acupuncture-related adverse reactions, outcome assessors will record adverse events (AEs) during and after each treatment. The frequency of AE occurrence will be analyzed and evaluated. In this trial, AEs are defined as follows: (1) Any clinically significant adverse medical event occurring in patients receiving EA or undergoing study procedures that deviates from the expected clinical course of sepsis patients. (2) Any clinically significant adverse medical event considered related to EA or the study procedure, regardless of its alignment with the expected clinical course of sepsis patients. “Response to EA” refers to an adverse event for which a causal relationship with EA cannot be excluded.

In this study, acupuncturists evaluated the safety of acupuncture, and any AEs associated with acupuncture, including bleeding, subcutaneous hemorrhage, serious pain, local infection, and other unexpected adverse reactions, were documented. If AEs occur, the EA or sham EA ends, and experienced ICU doctors and acupuncturists promptly take necessary steps to ensure patient well-being.

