### Data Collection and Management

Within 24 h of consent confirmation, the investigators will perform baseline assessments and collect necessary demographic and epidemiological data from the medical records system. Record forms will record information such as age, sex, weight, height, medical history, ICU admission source and classification, infection source, pathogen type, vital signs, baseline SOFA score, and relevant biomarkers.

During the treatment period, all of the aforementioned outcome measures and safety indicators will be recorded. All the reasons for and details of participant discontinuation or withdrawal will also be systematically recorded. All paper-based data will be documented in the case report form (CRF).

Data will be managed through the Tongji Hospital YiDuCloud Follow-Up Platform. Team members have generated electronic case report form (eCRF) on the basis of paper reports and annotations. The data collected from the CRFs will be entered into the system by an investigator.

Upon data submission, the database will be locked. Any postlock modifications must receive principal investigator approval, be signed off by the data entry staff, and be recorded by the system. All records, both paper and electronic, will be retained for at least five years after publication.

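### Table 1 schedules adverse event recording on days 1-6 only, so none is scheduled after the day of the last session, although patients are assessed to day 9 and followed to day 28

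*Protocol article*

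**What the plan says.** All references are to the protocol article.

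- **Table 1.** The AE row has crosses on days 1 to 6, the same columns as the EA and sham EA rows. Its cells for days 7, 8, 9 and 28 are empty. The SOFA rows have crosses through day 9, biomarkers are taken on day 7, and mortality and the support-free-day outcomes are marked at day 28.
- **EA Group.** "Participants will receive EA sessions once daily for 6 consecutive days".
- **Study Design.** The trial has "6 days of postrandomization treatment, and a 22-day follow-up period".
- **Secondary Endpoints.** "Participants will be followed up until day 28 after randomization".
- **Interventions.** Adverse reactions are entered on the acupuncture record form after each session.
- **Safety Assessments.** "outcome assessors will record adverse events (AEs) during and after each treatment". No last day is given. Local infection is among the events listed: "any AEs associated with acupuncture, including bleeding, subcutaneous hemorrhage, serious pain, local infection, and other unexpected adverse reactions, were documented".
- **Data Collection and Management.** "During the treatment period, all of the aforementioned outcome measures and safety indicators will be recorded".
- **Abstract.** Safety is named as an aim next to efficacy.

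**The concern.** The scheduled AE window closes on the day of the last exposure. An event that first shows on day 7 or later has no scheduled place to be recorded, even though the patient is still assessed daily to day 9 and outcomes are collected again at day 28. Efficacy is thus looked for over a longer period than harm.

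This matters most for harms caused by the needle itself. EA needles go 20 to 30 mm deep at two acupoints on both sides, whereas the sham uses a non-insertive needle. A needle-site infection can therefore arise from the study procedure only in the EA arm, and the protocol names local infection as an event to be documented. At stake is how complete the safety description is. The primary analysis is not affected.

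**Working it through.** No power or alpha formula applies. The check is a count of days from Table 1 and the text.

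**1. The plan's own total.** Study Design gives 6 treatment days and 22 follow-up days: 6 + 22 = 28. This agrees with follow-up to day 28 under Secondary Endpoints.

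**2. Share of days with scheduled AE recording.** The AE row is marked on 6 days: 6 / 28 = 21%. Days without it: 28 - 6 = 22.

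**3. Later AE days after each session.** With sessions on days 1 to 6, a session on day *d* has (last AE day - *d*) later scheduled AE days.

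| Session day | AE row ends day 6 (as planned) | AE row ends day 9 (if extended) |
|---|---|---|
| 1 | 5 | 8 |
| 2 | 4 | 7 |
| 3 | 3 | 6 |
| 4 | 2 | 5 |
| 5 | 1 | 4 |
| 6 | 0 | 3 |
| Mean | 15 / 6 = 2.5 | 33 / 6 = 5.5 |

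Extending the row to day 9 would cover 9 / 28 = 32% of days.

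**4. Exposure.** Two acupoints on two sides make 4 needles per session, and 4 x 6 = 24 penetrations for a full EA course. This is a maximum, since some sessions may not be completed. It describes exposure and does not measure lost events.

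**5. Does the text widen the window?** Interventions ties the record to each session. Safety Assessments says during and after each treatment, without an end day. Data Collection and Management speaks of the treatment period. That last sentence cannot be read as strictly exclusive, because it also covers outcome measures that run to day 28. Even so, no section schedules AE recording after day 6, and Table 1, the only place with explicit days, stops there.

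**6. Who could still benefit from a change.** Trial Status reports 136 enrolled, of whom 129 have completed all visits. The number still to be enrolled depends on the final size:

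- 154 - 136 = 18 if the trial ends with the interim cohort
- 308 - 136 = 172 at the planned size
- 500 - 136 = 364 at the maximum

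**The case against.** The strongest case on the other side is that the window is stated openly, is the same in both arms, and validly describes AEs on days 1-6. The wording in Safety Assessments sets no end day, so it does not forbid later recording. Infections from early sessions that show by day 6 fall inside the window. Some serious consequences would surface elsewhere: SOFA to day 9, and mortality and the ICU-, hospital- and support-free days to day 28. All of this stands, and it limits the point to what is scheduled.

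A reader might infer more than the documents support:

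- *That delayed harms are missed.* They are not scheduled to be captured after day 6. Whether any go unrecorded is not known.
- *That needle-site infection usually appears days later.* The document gives neither onset time nor rate. The point needs only the assumption that some events first show after the day of the session.
- *That the safety comparison is biased towards no difference by a material amount.* Late needle-site events could be lost in one arm only, but no size can be computed, and the article states no comparative safety hypothesis.
- *That events are hidden from the data monitoring committee.* The Statistical Analysis section gives that committee the interim and sample size results. It does not say that AE data go to it.
- *That one arm's AEs go unanalysed.* Safety evaluation is already planned on the ITT population, which covers both arms.
- *That needle sites could simply be inspected at day 28.* No in-person visit is described for that day. Table 1 shows only mortality and the free-day and free-time outcomes.

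Nor is this detail that an article leaves to a fuller protocol: Table 1 fixes the days.

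**Conclusion.** The point holds in a limited form. AE recording is scheduled on 6 of 28 post-randomization days (21%) and ends on the day of the last session. After that session there are no later scheduled AE days, although three daily assessments (days 7-9) and a day-28 outcome collection already exist. AEs that first appear after day 6 are not scheduled to be captured. They include local infection, which can arise from needling only in the EA arm.

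This rests on Table 1 as printed, on sessions falling on days 1-6 as scheduled there, and on the assumption that some AEs first show later than the day of the session. The number of such events, and any effect on the comparison between arms, cannot be estimated from the documents. The change is a cheap improvement to how harms are captured, and nothing in the efficacy analysis depends on it.

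**What to change.** For patients still to be enrolled:

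1. Extend the AE row of Table 1 to days 7, 8 and 9, using the daily assessments already made for SOFA.
2. Collect serious AEs from records at the existing day-28 outcome collection.
3. State this window, with its end days, in Safety Assessments and in Data Collection and Management, identically for both arms.
4. Report AEs on days 1-6 for all patients, and report the extended window separately for those enrolled after the change.

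**Cost.** Table 1 and the case report form need rewording, and a few record checks are added at existing time points. Under Monitoring and Quality Control, a revised protocol goes back for ethics review. The trial would then hold two AE windows, because the 129 patients who have completed all visits cannot be assessed prospectively on days 7-9. The gain depends on how many patients remain: 172 to 364 if the trial continues past the interim analysis, but only 18 if it ends at 154.

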### Data Collection and Management

Within 24 h of consent confirmation, the investigators will perform baseline assessments and collect necessary demographic and epidemiological data from the medical records system. Record forms will record information such as age, sex, weight, height, medical history, ICU admission source and classification, infection source, pathogen type, vital signs, baseline SOFA score, and relevant biomarkers.

During the treatment period, all of the aforementioned outcome measures and safety indicators will be recorded. All the reasons for and details of participant discontinuation or withdrawal will also be systematically recorded. All paper-based data will be documented in the case report form (CRF).

Data will be managed through the Tongji Hospital YiDuCloud Follow-Up Platform. Team members have generated electronic case report form (eCRF) on the basis of paper reports and annotations. The data collected from the CRFs will be entered into the system by an investigator.

Upon data submission, the database will be locked. Any postlock modifications must receive principal investigator approval, be signed off by the data entry staff, and be recorded by the system. All records, both paper and electronic, will be retained for at least five years after publication.

### Monitoring and Quality Control

Experts from diverse fields, including acupuncture, intensive care, statistics, and public health, collaboratively developed the trial protocol. If revisions are necessary, an updated protocol will be resubmitted for ethics review.

To ensure study quality, a standardized training program will be provided to all team members prior to recruitment, covering patient screening methods, EA administration, data collection and entry, and an overview of the database. After initiation, regular monitoring is conducted. Quality control for this study will be conducted independently by designated personnel at Wuhan Jinyintan Hospital, a tertiary academic medical center that is not otherwise involved in the research, to evaluate safety parameters and ensure protocol compliance. Comprehensive audits were conducted at least semiannually, with random sampling covering no less than 50% of the total cases. Any data modifications will be traceable via the YiDuCloud Follow-Up Platform. Reasons and details for drop-outs or withdrawals will be documented.

All acupuncture interventions are conducted under continuous ICU monitoring to ensure compliance with the treatment protocol. Additionally, randomized video recordings of more than 30% of treatment sessions will be archived and maintained for two years following study completion to allow for quality control verification.

### Statistical Analysis Plan

#### Sample Size Calculation

The sample size for the study is determined on the basis of the power of the hypothesis test for the primary endpoint (a reduction in the SOFA total score on day 7 postrandomization). Given the limited prior data on the expected effect size, a conventional fixed sample size design would risk insufficient power or inefficient resource use. Therefore, this trial adopts a sequential design, allowing dynamic sample size adjustment based on conditional power re‑estimation at an interim analysis while strictly controlling the overall type I error. The calculation assumes a 1:1 group allocation, an expected mean reduction difference of 1.2 between the EA and sham-EA groups, a common standard deviation of 3.2, a one-sided type I error rate (α) of 2.5%, and 90% power (β = 0.10). On the basis of these parameters, a fixed-sample design requires 300 patients (150 per group).

A single interim analysis will be conducted after 50% of the planned patients have completed the day 7 assessment or discontinued the study. Stopping boundaries are designed to allow early termination for efficacy or futility (nonbinding) and will be determined using a Lan-DeMets spending function approximating O’Brien-Fleming boundaries [30]. Accounting for the group sequential design, the sample size inflation factor is 1.025, resulting in a total sample size of 308 patients (154 per group).

If the study does not stop at the interim analysis, sample size re-estimation will be performed by an unblinded statistician. Conditional power will be calculated on the basis of the observed between-group difference and standard deviation among the first 154 patients. If the conditional power is greater than or equal to 90%, enrollment will proceed to 308 patients. If the conditional power is less than 90%, the sample size may be increased to 500 participants, with a minimum of 308 participants retained. The final sample size will be determined on the basis of statistical considerations, budget, enrollment feasibility, and ethical factors.

#### Statistical Analysis

Statistical analysis will be performed using SAS (version 9.4 or higher) or other validated statistical software (e.g., R). The analysis will be based on predefined populations: the intention-to-treat (ITT) population, which includes all randomized participants who received at least one intervention, and the per protocol (PP) population, which is a subset of the ITT population excluding those with major protocol violations. Primary efficacy analyses will be conducted on both the ITT and PP populations, while baseline demographic data, secondary efficacy analyses, and safety evaluations will be based on the ITT population.

The primary hypothesis will be tested at a one-sided significance level of 0.025, and all other hypotheses will be tested at a two-sided significance level of 0.05. Confidence intervals will be reported at the 95% level. Continuous variables will be summarized using means, standard deviations, medians, and ranges, while categorical variables will be presented as counts and percentages.

The primary endpoint is the reduction in the SOFA score on day 7. The hypothesis is that compared with the sham-EA group, the EA group will have a greater reduction in SOFA score. This hypothesis will be tested using analysis of covariance (ANCOVA) to adjust for baseline SOFA scores.

The study uses an adaptive group sequential design, allowing for early stopping and sample size re-estimation while controlling Type I error inflation. The study is divided into two stages: Stage 1 includes the first 154 randomized subjects for interim analysis, and Stage 2 includes all subsequent subjects. ANCOVA models are applied to each stage separately to estimate Z-statistics, defined as Zᵢ = $$\frac{{\widehat{\delta }}_{i}}{se\left({\widehat{\delta }}_{i}\right)}$$ (*i* = 1, 2), where $${\widehat{\delta }}_{i}$$ is the estimated least squares mean difference and $$se\left({\widehat{\delta }}_{i}\right)$$ is the standard error.

At the interim analysis, a one-sided *P* value (*P*₁) will be calculated on the basis of Stage 1 data. If *P*₁ is less than 0.0015, the study can stop early for efficacy. If *P*₁ exceeds 0.3947, the study may stop for futility. However, since the futility boundary is nonbinding, enrollment may continue without inflating Type I error. If the study proceeds after the interim analysis, Stage 1 and Stage 2 populations will be analyzed separately to obtain Z₁ and Z₂, and a combined weighted statistic Z = $${w}_{1}{Z}_{1}+{w}_{2}{Z}_{2}$$ will be calculated, where $${w}_{1}={w}_{2}=\sqrt{0.5}$$ [31]. The final one-sided *P* value derived from Z is 0.0245; if it is less than 0.0245, the null hypothesis is rejected.

In this trial, interim analysis data will be extracted by an independent researcher who is not involved in participant recruitment, randomization, follow‑up, or data entry. Sample size re‑estimation will then be performed by a separate independent unblinded statistician. The results will be reported solely to an independent data monitoring committee (DMC). The study team and clinical staff will remain blinded to the interim results. Unblinded statisticians cannot participate in subsequent protocol amendments, and the DMC may recommend sample size adjustments without disclosing specific results.

For missing data at the primary endpoint, if a patient dies within 7 days, the SOFA score on the day of death will be set to 24 (the highest possible score), and the SOFA score on subsequent days will also be set to 24. Other missing values in the primary endpoint will be imputed using the multiple imputation (MI) method.

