**Methods:**

In this single-center, randomized, sham-controlled clinical trial, an adaptive sample size of 154–500 patients diagnosed with sepsis will be included. Eligible patients will be randomly assigned to receive EA or sham EA treatment at a 1:1 ratio using block randomization. Patients in the two groups will receive 6 consecutive sessions of 30-min EA or sham EA treatment, with the initial acupuncture treatment being completed within 24 h after randomization. The primary outcome is the change in the total score of the Sepsis-Related Sequential Organ Failure Assessment (SOFA) on day 7 after randomization compared with baseline. Secondary outcomes include changes in the SOFA score and related serological outcomes, mortality, ICU-free days, hospital-free days and organ support-free days from baseline to day 28. Statistical analyses will be performed on a full analysis set (FAS) and a per-protocol set (PPS).

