### Randomization and Allocation Concealment

Eligible participants will be randomly assigned to the EA group or the sham-EA group at a ratio of 1:1 through dynamic block randomization. Computer-generated randomization sequences will be produced by an independent investigator and secured in sequentially numbered, opaque, sealed envelopes. Afterward, a nonblinded acupuncturist will access the allocation assignment by opening envelopes in sequential order and subsequently administering the corresponding intervention. To maintain blinding in patients, outcome assessors, and statisticians, the allocation sequence will be concealed until the end of the study.

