#### ICU Standard Therapy

All participants received standard ICU therapy, which was developed on the basis of expert consensus [28]. Routine treatment includes source control of infection, antibiotics and/or other anti-infective measures, sedation and analgesia, fluid management, mechanical ventilation, renal replacement therapy, nutritional support and so forth. EA sessions will be scheduled within a flexible daily window, coordinated with bedside staff. Routine ICU care and emergency procedures take priority. If a session cannot be completed because of prone positioning or other interventions, it will be recorded as a protocol deviation.

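### The population called ITT leaves out randomised patients who received no session, and entry to it is settled after the person delivering treatment knows the allocation

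*Protocol article*

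**What the plan says.** The Protocol article, Statistical Analysis, names two populations. The first is "the intention-to-treat (ITT) population, which includes all randomized participants who received at least one intervention". The second, per protocol, is the first minus major violators. The plan then states: "Primary efficacy analyses will be conducted on both the ITT and PP populations". Baseline, secondary efficacy and safety analyses use the first set alone. All-cause mortality at day 28 is a secondary endpoint, so it falls under the same definition.

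Under Randomization and Allocation Concealment, "a nonblinded acupuncturist will access the allocation assignment by opening envelopes in sequential order and subsequently administering the corresponding intervention".

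The same Statistical Analysis section sets the death rule: "if a patient dies within 7 days, the SOFA score on the day of death will be set to 24 (the highest possible score"), and later days also take 24.

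The abstract uses other names: "Statistical analyses will be performed on a full analysis set (FAS) and a per-protocol set (PPS"). It does not define these sets.

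**The concern.** A set that requires at least one session is conditioned on something that happens after randomisation. That is usually defensible when the start of treatment cannot depend on the arm. Here the patient, the assessor and the statistician are blinded, but the person who gives the qualifying session is not. Blinding elsewhere does not protect this step.

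There is time for a patient to be lost. Table 1 puts randomisation on day 0 and the first session on day 1. The limit for the first session is given as "the initial acupuncture treatment being completed within 24 h after randomization" in the abstract and "the initial acupuncture treatment should be administered within 12 h post-randomization" under Study Design. During that time, "Routine ICU care and emergency procedures take priority".

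The arms also differ in what is done. The EA group is needled 20 to 30 mm deep with current; the sham group has neither penetration nor current. A reason for not starting could therefore arise more often in one arm. That is an inference, not something the protocol states.

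At stake are the randomised comparison itself and the reach of the death rule. A patient who dies before any session would carry the worst possible score, yet is outside every efficacy set that the plan names. No planned analysis would show what the exclusion did.

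**Working it through.** **1. Who is in and who is out, by the plan's own wording**

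| Randomised patient | In the set called ITT? | Death rule applies? |
|---|---|---|
| Receives any of the six sessions, survives to day 7 | Yes | Not needed |
| Misses the first session, receives a later one | Yes | Yes, if death is within 7 days |
| Receives a session, dies within 7 days | Yes | Yes, scored 24 |
| Dies before any session | No | Never reached |
| Survives but receives none of the six sessions | No | Not needed, but the outcome is left out |

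Only the last two rows are lost.

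**2. The plan's own sample size, reproduced first**

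Inputs from Sample Size Calculation: difference 1.2, SD 3.2, one-sided 0.025, power 90%, 1:1.

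n per group = 2 × (1.960 + 1.282)² × 3.2² / 1.2² ≈ 149.4, so 150 per group and 300 in total. Then 300 × 1.025 = 307.5, so 308, or 154 per group. The sample size is not in error, and the fix does not change it.

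**3. Illustration of the shift**

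The document gives no mean baseline SOFA, no mean change and no count of untreated patients. Assumptions: mean baseline 6 to 12, and a mean change of −2 to −4 in the other patients.

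Gap = (24 − baseline) − mean change in the others.
- Smallest: (24 − 12) − (−2) = 14.
- Largest: (24 − 6) − (−4) = 22.

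If k more early deaths are dropped from one arm of 154 than from the other, the unadjusted difference shifts by k × gap / 154.

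| Excess deaths dropped, k | Gap 14 | Gap 22 |
|---|---|---|
| 1 | 0.09 | 0.14 |
| 3 | 0.27 | 0.43 |
| 5 | 0.45 | 0.71 |

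Three give 0.27/1.2 = 23% to 0.43/1.2 = 36% of the planned effect. Producing the whole 1.2 would take 1.2 × 154/22 = 8.4 to 1.2 × 154/14 = 13.2 excess deaths.

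At the interim, with about 154/2 = 77 per arm, one excess death shifts the difference by 14/77 = 0.18 to 22/77 = 0.29 points. That analysis drives both stopping rules and the sample size re-estimation.

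**4. Effect on the error rate under the same assumptions**

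With no true effect and a single look at one-sided 0.025, the error rate is 1 − Φ(1.96 − shift/SE). With SD 3.2, SE = 3.2 × √(2/154) = 0.365.

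| Excess deaths dropped from EA only | SD 3.2 | SD widened for other deaths scored 24 (assumed 2% to 10% by day 7) |
|---|---|---|
| 1 | 0.044 to 0.058 | 0.035 to 0.047 |
| 3 | 0.113 to 0.216 | 0.067 to 0.134 |

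This simplifies the two-stage test and shows scale only. Dropping the same deaths from sham only would shift the estimate the other way.

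**5. Mortality**

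Each death left out of one arm of 154 is 1/154, about 0.6 percentage points of that arm's 28-day mortality.

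**The case against.** The best defence is that few patients can be affected. Eligibility excludes those expected to survive less than 7 days or to stay in the ICU less than 48 h, and it removes local bleeding, skin damage, leg trauma and implanted devices from both arms. Six sessions are planned and any one of them keeps a patient in. The document reports no untreated patients and no imbalance. All of this stands, and it limits the probable size. It does not supply the missing analysis.

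Several stronger readings are tempting and are not supported:

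- *The acupuncturist decides who is treated.* The protocol gives this person the envelope and the needles. Sessions are coordinated with bedside staff. Knowledge of allocation is documented; authority to withhold is not. The time between opening the envelope and the session is also not stated, and a death before opening could not depend on knowledge of the arm.
- *Deterioration or a displaced first session removes a patient.* It does not. A session that cannot be completed is recorded as a protocol deviation, and a later session keeps the patient in.
- *The set removes exactly the patients scored 24.* It removes only deaths before any session. Other deaths within 7 days stay in.
- *There is a gap of 12 to 24 h before treatment.* These are two conflicting upper limits, not an interval. The passages must be reconciled.
- *Defining Stage 1 by the first 154 randomised contradicts the treated-only set.* That wording assigns patients to stages, and an analysis set can be applied within each. It needs a clarifying line, no more.
- *The result will favour EA.* Nothing in the document shows a direction.

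**Conclusion.** The point holds in a limited form. A modified ITT set carries the name ITT, it is the widest set in any named efficacy analysis, and entry to it is settled after the person delivering treatment knows the arm. Because of that last feature this is more than a preference between analysis sets. The abstract's undefined FAS does not repair it.

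The actual bias is unknown in size and direction and may be nil. The figures above rest on an assumed gap of 14 to 22 points and on losses confined to one arm, neither of which comes from the document. They show only that, because a death scores 24, a handful of one-sided losses would be material against a target of 1.2, while a count large enough to create the whole effect looks unlikely given the eligibility criteria.

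**What to change.** Define ITT (or FAS) as all randomised patients, analysed as allocated, whether or not a session was given. Apply the death score to all of them. Use this set for the primary, secondary and mortality analyses and for both stage statistics, and say so where Stage 1 is defined. Keep the treated-only set for safety, and as a sensitivity analysis labelled modified ITT. Use one set of names in the abstract and in Statistical Analysis. Report by arm how many patients received no session, and why.

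Cost: planned N stays at 308. Including untreated patients may dilute the effect slightly, and their day 7 and day 28 outcomes must be collected. The change is a protocol revision, which Monitoring and Quality Control says goes back for ethics review. It is best made before the interim analysis, by people who have not seen unblinded data. Trial Status reports 136 enrolled, below the 154 on which the interim analysis rests.
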